### Study Measurements

#### End Points

The duration of the intervention is 6 weeks with 12 weeks of follow-up. Outcome measures were collected at baseline T1, end of intervention (week 6) T2, week 12 (T3), and week 18 (T4; Figure 2). The primary endpoint is the change in self-reported ST (total ST and SB characteristics, such as screen-based ST, longest continuous ST, and number of sedentary bouts ≤30 min). Secondary endpoints include the changes in step count (steps/d), time spent in LPA (min/wk), time spent in MVPA (min/wk), the Short Physical Performance Battery (SPPB) score, blood pressure, Measuring Change in Physical Activity Questionnaire (MCPAQ) score, waist circumference, BMI, and quality of life (SF-12v2 score) (Table 2).

**Figure 2. F2:**
[figure not shown]
CONSORT flow diagram.

**Table 2. T2:** Participant schedule of enrollment, interventions, and assessments.

	Study period				
	Enrollment	Baseline assessment/allocation	Post allocation		
Timepoint	T0	T1	T2 6 wk	T3 12 wk	T4 18 wk
Eligibility screen	×				
Informed consent	×				
Allocation		×			
Interventions					
CON group					
INT group					
Assessments					
Sociodemographics		×			
Primary outcomes					
Sedentary time (total sedentary time and sedentary behavior characteristics)		×	×	×	×
Secondary outcomes					
Step count (Omron HJ-204)		×	×	×	×
Time spent in LPA/MVPA (IPAQ-S-C)		×	×	×	×
Measuring Change in Physical Activity questionnaire (MCPAQ)		×	×	×	×
Physical function (SPPB)		×	×	×	×
Quality of life (SF-12)		×	×	×	×
BMI		×	×	×	×
Waist circumference		×	×	×	×
Blood pressure		×	×	×	×

a SF-12: Short-Form Health Survey-12.

#### Measurements

A self-developed questionnaire will be used to investigate the sociodemographic and clinical information of the participants, including age, gender, ethnicity, educational level, marital status, illness, residence, risk of falls, frailty status, current employment status, and availability of exercise areas in the vicinity of the residence.

##### ST and PA

The International Physical Activity Questionnaire Short version Chinese (IPAQ-S-C) was used to assess participants’ levels of PA and SB over the past 7 days. It consists of vigorous intensity, moderate intensity, walking (light intensity), and ST, with a total of 7 items. Qu et al [51] conducted a cross-cultural adaptation to form a Chinese version of the IPAQ. The reliability and validity of the Chinese version of the questionnaire were favorable. Total ST was recorded as the average amount of time participants spent in sitting, lying, and semi-lying postures each waking hour. When participants have difficulty recalling total ST, recall will be aided by possible sedentary scenarios in a “typical day,” such as calculating the total amount of ST spent daily in transportation, hobbies, watching TV, smartphones and computers, socializing, reading, eating, and any other SBs.

SB characteristics, including screen-based ST, longest continuous ST, and number of sedentary bouts lasting ≤30 minutes, were obtained through a self-developed questionnaire. Screen-based ST was recorded as ST occurring in situations such as watching television and using mobile phones, computers, and other similar electronic devices.

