Dunstan et al [25] in their study “Sitting Less and Moving More” suggest that sedentary lifestyle can be addressed through a “staircase approach” (Figure 1). This is a promising but understudied approach. It involves modest transition steps: first emphasizing the reduction of SB, decreasing overall sitting time, and breaking up ST by increasing standing and activity; then gradually increasing LPA to provide a “preparation base” for the long-term transition to higher-intensity PA, for example, walking, engaging in family leisure activities, flexibility training, strength training, etc; finally, gradually engaging in sufficient MVPA, such as brisk walking or jogging, dancing, tai chi, handball, water sports, etc, to meet the amount of PA above the guideline level [41]. Compared to accumulating weekly amounts of MVPA, interventions of the beginning stage aimed at reducing SB may seem more appealing and be easier for older adults to integrate into their daily lives [42]. Reducing SB may be an essential initial step toward implementing sustainable changes in movement patterns, which would support higher levels of overall PA and thus be beneficial to health.

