### Participants

Participants for this study were recruited through posters and leaflets distributed at 2 community health service centers in Changchun City, Jilin Province, China, from March 2024 to October 2024. All participants signed informed consent before the baseline outcome assessment. The following are the inclusion and exclusion criteria for participants:

Inclusion criteria:

Older adults aged ≥65 years.Residents living in the community for ≥6 months.Sedentary lifestyle (ie, more than 6 h of time awake spent in a sitting or reclining posture per day and PI: MVPA ≦150 min/wk) for at least 6 months.Able to walk 100 m without assistance.Informed consent and voluntary participation in this study.

Exclusion criteria:

Severe physical illness or long-term bedridden.Unable or unwilling to communicate with researchers.Participating in other PA or SB intervention programs.Severe cardiovascular and cerebral vascular diseases that require restriction of activities.Severe muscle weakness, skeletal diseases, or deformities that lead to restriction of PA.Depression, schizophrenia, and other psychiatric disorders or dementia that led to severe cognitive impairment.History of central nervous dysfunction, such as mild hemiplegia, spinal cord disease, and cerebral ataxia.

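### The secondary endpoint called LPA is in effect walking time, which does not match the protocol's own light and moderate-to-vigorous steps

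*Protocol article*

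**What the plan says.** Under End Points, the protocol article lists two separate secondary endpoints, "time spent in LPA (min/wk), time spent in MVPA (min/wk"). Table 2 gives a single source for both: "Time spent in LPA/MVPA (IPAQ-S-C"). The section ST and PA describes that questionnaire: "It consists of vigorous intensity, moderate intensity, walking (light intensity), and ST, with a total of 7 items". It gives no split of walking by pace and no rule for brisk walking.

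The Introduction sets out the staircase on which the intervention is built. Its examples for the LPA step are "for example, walking, engaging in family leisure activities, flexibility training, strength training". Its last step is described as "finally, gradually engaging in sufficient MVPA, such as brisk walking or jogging, dancing, tai chi, handball, water sports, etc".

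Study Interventions assigns replacement of sitting by LPA to Phase II and the increase in MVPA to Phase III. Table 1 shows that Phase III recommends several forms of exercise: aerobic, plyometric, balance and flexibility training.

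**The concern.** The same behaviour, brisk walking, belongs to the MVPA step in the intervention model but appears to fall under the light component in the measurement. The variable called LPA would then be too broad, because it includes brisk walking, and too narrow, because it leaves out light activity that is not walking.

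What is at stake is the reading of the intensity gradient. The abstract's conclusions and Strengths and Limitations both describe a passage from standing to LPA and on to MVPA. Among the listed outcomes, only the LPA and MVPA times separate those steps by intensity. The pedometer gives average steps per day and no pace, so it cannot make the distinction. If walking minutes are read as LPA, a real gain at the last step could appear as a gain at the step before it, or not appear at all.

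**Working it through.** **The plan's own figure.** The article states no effect size or precision for LPA or MVPA. Its only computed design figure concerns sedentary time: 120/142.98 = 0.839. A two-sided unpaired t test at 5% with 80% power then needs 23.3 per group, so 24, as stated (power 0.81 at 24). This does not depend on how walking is classed.

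**The texts side by side.**

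| Activity | Introduction (staircase) | ST and PA with Table 2 |
|---|---|---|
| Walking, pace not given | LPA step | walking component, labelled light |
| Brisk walking | MVPA step | walking component, if reported there |
| Family leisure, flexibility, strength training | LPA step | no light component to hold it |
| Jogging, dancing, tai chi and similar | MVPA step | moderate or vigorous component |

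The second and third rows do not agree. The article gives no formula for LPA minutes. By elimination, though, walking is the only component labelled light, so LPA = walking minutes (W) and MVPA = moderate (M) plus vigorous (V) minutes.

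**Direction of the error.** Let G be a true MVPA gain that replaces sitting, and w the share of it that is brisk walking reported under the walking item.

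- Recorded MVPA gain = G(1 − w)
- Gain wrongly recorded as LPA = Gw

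The documents give neither G nor w. Purely to show the mechanism, assume G = 60 min/wk and let w run over its whole range:

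| w | Recorded MVPA gain (min/wk) | Recorded as LPA (min/wk) |
|---|---|---|
| 0 | 60 | 0 |
| 0.25 | 45 | 15 |
| 0.5 | 30 | 30 |
| 0.75 | 15 | 45 |
| 1 | 0 | 60 |

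A participant who moves from slow to brisk walking for the same number of minutes changes neither W nor M + V, so neither endpoint moves.

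**What the summed endpoint can show.** At any visit, if the reports are accurate and the moderate and vigorous items hold no light activity, M + V ≤ true MVPA ≤ W + M + V. The upper limit is loose because W includes slow walking. The limit applies to minutes at a visit. It does not strictly bound a change from baseline: in the slow-to-brisk case the sum changes by 0 while true MVPA rises.

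**The case against.** Four objections have weight.

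1. **The classification is inferred.** The article describes the questionnaire in one line and does not quote the items, so some participants may enter brisk walking under the moderate item. This stands. The misclassification may be partial and may differ between participants, which is why the conclusion is conditional on where brisk walking is reported.
2. **The conflict is narrower than it looks.** The Introduction puts plain walking in the LPA step, which agrees with the questionnaire label, and the staircase there summarises a cited concept. Neither Table 1 nor the phase descriptions name brisk walking. This stands in part: the handling of brisk walking is unstated, not expressly assigned to LPA. But the staircase is the declared basis of the three phases, and its LPA examples go beyond walking, so the label LPA still does not fit.
3. **The consequence is limited.** Two secondary endpoints are involved. Anticipated Findings names MVPA but not LPA, and for MVPA the error in the worked case runs against the intervention. This stands.
4. **The summed endpoint has the opposite fault.** It counts slow walking with MVPA. This also stands, and it can serve only as an upper bound.

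A reader might infer more than the documents support:

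- **That MVPA misses whatever Phase III produces.** Phase III recommends several forms of exercise, and nothing shown prevents jogging, dancing or structured training from being recorded as moderate or vigorous. Only the brisk-walking part is at risk.
- **That the understatement can be given as a percentage.** The documents contain no brisk-walking share.
- **That regular brisk walkers entered the trial as inactive under "MVPA ≦150 min/wk".** Participants does not name the screening instrument, and Table 2 lists the IPAQ from baseline, after the eligibility screen.

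**Conclusion.** The point holds as a mismatch between label and measurement. As described, the LPA endpoint is walking time. It does not correspond to the protocol's own LPA step, and the MVPA endpoint leaves out brisk walking to whatever extent it is reported under the walking item. Light activity other than walking is not captured as LPA.

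The direction follows from the text: where brisk walking replaces sitting, MVPA is understated and LPA overstated by the same minutes. The size is unknown and could be nil if brisk walking is entered under the moderate item. The conclusion assumes that LPA is the walking item alone, since the article names no other light component. Sedentary time, step count and the sample size are unaffected. What is limited is any statement about which intensity step of the staircase worked.

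**What to change.** - Reconcile the Introduction with ST and PA, and state how brisk walking was reported and scored.
- Report the endpoint as walking time (min/wk) instead of LPA, and keep MVPA as moderate plus vigorous minutes.
- Add one sensitivity analysis of walking plus moderate plus vigorous minutes, using the same generalized estimating equation model. Present it as an upper bound on MVPA minutes because it includes slow walking, and note that it need not bound the change from baseline. Results states that data collection was complete by May 2025, so date the addition and disclose it as specified after data collection.
- Draw no conclusion about the LPA step versus the MVPA step from the walking item alone.

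The cost is a relabelling, a sentence on scoring and one extra model on data already collected. The downside is that the claim about LPA becomes a claim about walking. With collection finished, walking pace cannot be recovered, so the analysis can mark the ambiguity but cannot remove it.

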##### Step Count

Participants’ PA will be monitored by using Omron HJ-204 pedometers, which collect the average number of steps taken over 7 days, in steps per day. Participants will be asked to wear the pedometer over their hip and to record the number of steps in the activities diary before going to bed.

##### Measuring Change in PA

The MCPAQ was developed by Nahar et al [52] based on an MTM with 29 items containing 2 subscales, initiation and maintenance. The questionnaire is based on a 5-point Likert scale, with values ranging from 0 (never) to 4 (completely sure). The initiation model consists of 3 constructs: participatory dialogue (10 items), behavioral confidence (5 items), and changes in physical environment (3 items). The maintenance model consists of emotional transformation (3 items), practice for change (3 items), and changes in social environment (3 items). The higher the total score for each item, the greater the likelihood that participants will initiate or maintain changes in PA. Yang et al [53] conducted a cross-cultural adaptation to develop the Chinese version of the MCPAQ. The Chinese version of the MCPAQ has shown good reliability and validity in Chinese older adults with hypertension. The total scale Cronbach *α*=0.911, the subscales ranged from 0.729 to 0.943, and the test-retest reliability was 0.898.

##### Physical Function

SPPB will measure participants’ physical function [54], which combines balance, gait speed, and leg strength into a single score from 0 (worst) to 12 (best). Meaningful clinical change is considered 1 point for the SPPB [55]. A total score of <10 is considered frailty, as well as a high risk of disability and falls. For increased PA, participants were categorized based on SPPB scores at baseline to recommend a personalized Vivifrail multicomponent exercise program at phase III [56].

##### Quality of Life

Participants’ quality of life will be assessed with the Chinese version of the Short-Form Health Survey-12-Version 2 (SF-12v2), one of the common measurement tools for evaluating health-related quality of life from the patient’s perspective [57]. The scale has demonstrated high reliability and validity in evaluating the health status of Chinese older adults [58,59]. The scale consists of 12 items, including 8 dimensions, which are physical functioning (2 items), role physical (2 items), bodily pain (1 item), general health (1 item), vitality (1 item), social functioning (1 item), role emotional (2 items), and mental health (2 items). The first 4 dimensions are within the physical health composite scale, and the rest are part of the mental health composite scale. It is recommended to use the total scores of the physical and mental composite scale, with a mean score of 50 (SD 10).

##### Anthropometric Parameters

Anthropometric parameters included height, weight, waist circumference, BMI, and blood pressure. Each data collection will be repeated twice using the same measuring tool, and the average value recorded will be rounded to one decimal.

##### Blood Pressure

Avoid strenuous exercise or workout within 1 hour before measurement. The participants will sit still for 5 to 10 minutes; the mercury sphygmomanometer is used to measure the systolic and diastolic blood pressure.

##### Adherence

The weekly sessions and interventions will be repeated 2 to 4 times in the community health center to avoid scheduling conflicts for participants and to ensure compliance. The percentage of participants who attend sessions and activities will be recorded (total number of activities/actual number of sessions attended). Participants’ satisfaction with the intervention will be assessed by rating the study on a scale of 1 to 10.

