c LPA: light-intensity physical activity.

d PA: physical activity.

e TV: television.

f ST: sedentary time.

g MVPA: moderate-to-vigorous-intensity physical activity.

h PI: physical inactivity.

i WHO: World Health Organization.

The program for the intervention group will follow the staircase approach in the rhythm of the reduction of ST and interruption of SB through standing and moving, followed by gradual replacement of SB with LPA, and ultimately leading to increased PA and modification of a sedentary lifestyle. During weeks 1‐2, “Phase I: Sitting Less” will be implemented. This phase includes a discussion of advantages and disadvantages, thematic session on SB change, Healthy Behavior Manual, and SB interruption interventions. This component involves recognition of SB and reduction and interruption of SB through standing and activities. “Phase II: Moving More” will be implemented during weeks 3‐4. The interventions will include warning stickers, pedometer-based interventions, and activities diary. This component involves the gradual replacement of SB with LPA. “Phase III: Increasing Physical Activity and Modifying Sedentary Lifestyle” will be implemented during weeks 5‐6. The interventions will include thematic sessions on PA, introduction to health and fitness resources, and social support. This intervention aims to increase and maintain the amount of MVPA among participants. They will be encouraged to engage in all stages of the intervention, and data will also be incorporated if the participants stay at any stage of the staircase lifestyle change intervention, provided that they have attended phase I (weeks 1‐2); otherwise, they are deemed to have withdrawn.

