### Dropout and Withdrawal

Participants can withdraw at any time for any reason. They can also choose to remove their data from the study. Participants will be regarded as having withdrawn if they request to leave the trial or are lost to follow-up. Participants in the intervention group will be regarded as having withdrawn if they no longer participate in the behavior change intervention that differed from those in the control group. As this research assumes that each stage of the staircase intervention generates health effects, participants will be allowed to skip a stage but will be expected to complete the first stage and be considered to have withdrawn if they do not.

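### The attendance ratio in the Adherence section is upside down and does not match its label: a minor error of definition, to correct before the figure is reported

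*Protocol article*

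**What the plan says.** The Adherence section announces the measure in these words: "The percentage of participants who attend sessions and activities will be recorded". A parenthesis then gives the calculation: "total number of activities/actual number of sessions attended". Just before this, the section explains the scheduling: "The weekly sessions and interventions will be repeated 2 to 4 times in the community health center". The stated purpose is to prevent clashes with participants' other commitments and so to support compliance.

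Two other sections bear on how attendance is read. Under Dropout and Withdrawal, "participants will be allowed to skip a stage but will be expected to complete the first stage", and those in the intervention group who do not complete it count as withdrawn. Study Interventions adds that "data will also be incorporated if the participants stay at any stage of the staircase lifestyle change intervention", again provided that Phase I was attended.

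Adherence is not among the primary or secondary endpoints in the End Points section. It has no row in the assessment schedule (Table 2), and it enters no model under Statistical Analyses.

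**The concern.** An attendance rate should be bounded by 0% and 100% and should rise as people attend more. The stated ratio does the opposite: what was attended is in the denominator. The label adds a second difficulty. A percentage of participants is a count of people over a count of people. The parenthesis is a ratio of event counts, with activities above and sessions below. Turning the fraction over would not by itself settle which quantity is meant.

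What is at stake is the reported adherence figure. The article presents the programme as one that older adults can readily adhere to (abstract, Conclusions; Strengths and Limitations), so a reader of the results paper will look for that figure. According to the Results section, data collection is complete and the results paper is still to come, so the definition can be put right before the number is published.

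**Working it through.** The plan states no attendance figure, so there is nothing to reproduce. The check is of the formula itself.

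**Inputs**
- T = the total in the numerator (Adherence section). The article does not give it as one number, so 4, 6 and 10 are assumed for illustration.
- a = sessions attended, the denominator (Adherence section).
- Assumption: T and a are in the same unit and each distinct session is counted once, so a ≤ T.

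**Formulas**
- As written: 100 × T / a.
- Attendance as normally understood: p = a / T, reported as 100 × a / T.
- Hence the printed value is 100 × (1/p). Because a ≤ T, it is never below 100%, and it rises as a falls.

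**Results for any T**

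| True attendance p | As written (100/p) |
|---|---|
| 100% | 100% |
| 80% | 125% |
| 50% | 200% |

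**One session attended, by assumed T**

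| T | As written | Corrected |
|---|---|---|
| 4 | 400% | 25% |
| 6 | 600% | 16.7% |
| 10 | 1000% | 10% |

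The direction of the error does not depend on T.

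**Can a reader undo it by taking the reciprocal?** That depends on how the figure is summarized, which the article does not state. Suppose half the participants attend everything and half attend 50%, so that true mean attendance is (100 + 50)/2 = 75%.
- If the ratio is computed per participant and then averaged: (100 + 200)/2 = 150%, whose reciprocal is 66.7%, not 75%.
- If totals are pooled first: 2T / (T + T/2) = 2/1.5 = 133.3%, whose reciprocal is 75%.

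So the reciprocal recovers the right value only under pooling.

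**Label against formula.** Suppose every participant attends half the sessions. The percentage of participants who attended at least one is 100%. The mean share of sessions attended is 50%. The printed formula gives 200%. These are three different answers, and the text does not identify which is intended.

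**The case against.** The strongest reply is that this is an obvious slip with almost no consequence. A percentage of 125% or 200% would be noticed at once, nothing shows that the figure has been or will be computed this way, and adherence feeds no endpoint or model. That stands, and it is why the point is minor. It does not remove the point: this is the only definition of attendance in the article, and the mismatch of label and unit remains after the fraction is reversed. One could also read the slash as separating two recorded counts. The word percentage speaks against this, and on that reading no percentage is defined at all.

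A reader might infer more than the document supports, in four ways.

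- *That the lack of a table by phase is an error.* Skipping is allowed after Phase I, so a split would be informative. But the section does not say that only one overall figure will be given, and such tabulation is commonly left to a fuller protocol or analysis plan. Nor can component counts show that an overall figure would hide which phase was skipped. The text lists 4, 3 and 3 components, so skipping Phase II or Phase III would each give 7/10 = 70%. However, in Table 1 the Phase II items are stickers, a pedometer and a diary, allotted per person with no session length. If only the timed items aimed at participants are counted (20 and 60 minutes in Phase I, 90 and 30 minutes in Phase III), skipping Phase II gives 4/4 and skipping Phase III gives 2/4.
- *That repeated offerings inflate the total.* The repeats are alternative slots for the same content. Counting each as a separate obligation is not a natural reading.
- *That non-attenders make the measure undefined in practice.* Dividing by zero is undefined, but intervention participants who miss Phase I are deemed withdrawn, so the case hardly arises among those retained. The same section also treats as withdrawn those who "no longer participate in the behavior change intervention that differed from those in the control group".
- *That the trial's result is compromised.* It is not. The randomized comparison does not use this figure.

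**Conclusion.** The definition is wrong as written, and the point is minor. The inversion follows from the ratio alone. The exact 1/p relation assumes matching units and each session counted once. If activities and sessions are different units, the printed number still rises as attendance falls, but it is no longer exactly 1/p. The mismatch of label and formula is plain from the text. Confidence is high on these two matters and extends no further: the document gives no ground for saying that a published figure will be inverted, that a phase breakdown was required, or that any efficacy result is affected.

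**What to change.** Replace the parenthesis with a definition such as: for each participant, the number of distinct sessions attended divided by the number of distinct sessions offered, times 100, where alternative time slots for the same session count once. State how it is summarized across participants (for example mean and SD, or median and quartiles), and change the label from a percentage of participants to the percentage of sessions attended. If a share of participants is also wanted, define it separately, with the attendance threshold that counts.

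The cost is a one-line correction and a little re-tabulation of records that already exist, before the adherence figure appears in the results paper.

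Optionally, and only where the records allow, show attendance by phase with the numbers who skipped Phase II or Phase III. For Phase II, which in Table 1 consists mainly of materials for self-monitoring and prompting, attendance may be a poor measure of what was received.
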